### Strengths

To our knowledge, this was the first population-based osteoporosis prevention intervention that has attempted to intervene with diet and physical activity components as unique health behaviours, and the first that adopts a self-efficacy-based theoretical model to guide behavioural strategies for both health behaviours. The study was also unique in the selection of workplaces as a vehicle for the delivery of the interventions. While worksites have been a popular platform for health behaviour-directed disease prevention, none to date has focused on osteoporosis prevention. Worksites are also ideal setting for identifying higher risk population such as individuals with sedentary occupations.

The participatory components in the study were expected to strengthen the intervention efficacy. The study utilised baseline assessment both to tailor the interventions as well as for evaluation purposes.

The intervention treated calcium intake and physical activity as individual health behaviours. This is vital as the two behaviours have their unique characteristics and barriers and need to be addressed with very different strategies. The study was able to implement separate workshops for calcium intake and physical activity thus facilitating the development of unique strategies for each of the behaviours.

### Limitations

The outcomes measures in this study were all derived from self-reports, which may incur potential bias. Steps were taken in this study to ensure the self-report measurement tools in this study were valid and reliable for the study population. Nevertheless, the osteoporosis preventive potential of the intervention would be more accurately and precisely assessed using objective bone mass density or other biomarker measures. However, resource and feasibility limitations excluded these possibilities. This is an important consideration for future studies in this area.

This study utilised the social structure and existing infrastructure within workplaces to deliver the interventions, but it did not have the capacity to influence workplace policies and practices to address sedentarism at the organisational level. This is a limitation in the study and an important consideration for future research, as intervention strategies to reduce workplace sitting time are rapidly developing.

At the time of the study, published ICC values for the targeted outcome and mediators were either limited or absent. In the absence of published ICCs, we adopted a conservative approach of assuming large ICCs in the calculations. This might have inflated the required number of clusters. However, it is also possible that the study will be underpowered to account for potential confounding. We will publish the observed ICC values for calcium intake, physical activity measures and self-efficacy scores in the reporting of the main results of the study. A retrospective calculation of the number of clusters and power based on the actual observed ICCs will be reported to compare with the original estimates.

High attrition rate is often a problem in population based intervention studies. A higher dropout rate is anticipated in this study because of loss of subjects through work factors such resignation and corporate restructuring. In an attempt to maintain cluster sizes, there was deliberate over-recruitment of within cluster subjects by 30 percent. However, some degree of selection bias may occur if attrition is high.

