### Sample size calculation

Sample size calculations took into consideration the cluster randomisation design by incorporating the design effect into the calculation. The design effect was calculated based on a cluster size of 20 and the intracluster correlation coefficient (ICC) using the formula: Design Effect = 1 + (within cluster sample size −1) x ICC. In the absence of ICCs for the outcome measures, available population standard deviations were used to calculate the variances and the ICC using the formula: ICC = variance between cluster/(variance between cluster + variance within cluster). In this study, there were two primary outcome measures, calcium intake and physical activity. Sample size calculations were carried out for both measures. Calculations were based on α = 0.05 and β = 0.1. Table 
1 shows the parameters used for calculating the number of clusters and the total number of participants. The study deliberately planned to over recruit within clusters to factor in a 30% attrition rate.

**Table 1 T1:** Summary of parameters used in the sample size calculation

**Outcome measures and mediators**	**Effect size**	**ICC used in sample size calculation**	**Standard deviation used in sample size calculation**	**Design effect**	**Number of clusters**	**Total subjects to be recruited**	
						**Before factoring in 30%****attrition**	**After factoring in 30%****attrition**
Calcium intake (milligrams per day)	250 milligrams	0.5*	290 milligrams***	10.5	14.7	294	480
Physical activity duration (minutes per week)	60 minutes	0.05**	150 minutes****	1.95	13	255	420

*Calculated using standard deviation from National Nutrition Survey 1998 and based on conservative estimates of inter- and intra-cluster variance
[23].

**Based on estimates from published studies
[30,31].

***Estimate from National Nutrition Survey 1998
[32].

****Based on estimates from published studies
[33,34].

The number of clusters required was different for each outcome measure, so the study was based on the highest number of clusters required, which was that for calcium intake (14.7). This was rounded up to 16 to ensure equal cluster numbers in both arms of this study.

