There was an error in the final step of this study's sample size calculations. The calculation did not double the sample size calculation that yielded the number of required subjects per arm (for this two-arm study). The sample size calculation, however, was very conservative with the ICC estimates and the study was expected to be overpowered despite the omission of this step. This study still has 90% power to detect 355 milligrams increase in calcium intake and 85 minutes increase in moderate to vigorous intensity physical activity with 16 clusters of 20 participants per cluster.

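### The claim that conservative ICCs leave the study overpowered despite the missed doubling is supported for calcium only; at its own ICC of 0.05, physical activity has about 66–73% unadjusted power for 60 minutes

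*Protocol article*

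**What the plan says.** The Sample size calculation section of the protocol article names two primary outcomes, calcium intake and physical activity, and sizes the trial for each. "Calculations were based on α = 0.05 and β = 0.1"; "The design effect was calculated based on a cluster size of 20". Table 1 gives:

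- **Calcium intake:** effect 250 mg, SD 290 mg, ICC 0.5, footnoted as resting on conservative variance estimates; 14.7 clusters, 294 subjects before attrition.
- **Physical activity:** effect 60 minutes per week, SD 150 minutes, ICC 0.05, footnoted "Based on estimates from published studies"; 13 clusters, 255 subjects before attrition.

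The larger requirement was adopted: "The number of clusters required was different for each outcome measure, so the study was based on the highest number of clusters required". The 14.7 was rounded up to 16.

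The paragraph after Table 1 discloses that these are per-arm figures that were not doubled. It then reassures the reader: "The sample size calculation, however, was very conservative with the ICC estimates", and adds that the study was expected to be overpowered all the same. It closes by saying that 16 clusters of 20 have 90% power for 355 mg and 85 minutes.

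The Limitations section, after noting that published ICCs were scarce or lacking, says: "In the absence of published ICCs, we adopted a conservative approach of assuming large ICCs in the calculations". It continues: "This might have inflated the required number of clusters".

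**The concern.** The ICC argument is the article's only stated reason for leaving the missed doubling uncorrected, and it is made for the calculation as a whole. A generous ICC can offset a halved sample size only for the outcome to which it was applied. Table 1 shows a large, deliberately cautious value for calcium. For activity it shows a value ten times smaller, drawn from published work and not described as conservative. Slack in the calcium ICC does nothing for activity, because the variance of the activity comparison depends on the activity ICC alone.

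The study hypothesis covers both behaviours. A reader told that the trial is overpowered could give a null activity result more weight than the design supports. The retrospective comparison of observed with assumed ICCs, promised in the Limitations section, would also start from an inaccurate description of what was assumed for activity.

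**Working it through.** **Inputs.** All come from the Sample size calculation section and Table 1: alpha 0.05, power 90%, cluster size m = 20, and the effects, SDs and ICCs listed above. Sidedness is not stated. Two-sided is assumed because it reproduces Table 1, whereas one-sided gives 209 subjects and 10.4 clusters for activity.

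**Step 1. Reproduce Table 1.** The plan's formula is "Design Effect = 1 + (within cluster sample size −1) x ICC". The number per arm is 2 × (SD × (1.960 + 1.282)/effect)² × design effect.

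- Activity: design effect 1 + 19 × 0.05 = 1.95. Unclustered n = 131.3 per arm; × 1.95 = 256.1; ÷ 20 = 12.8 clusters per arm (Table 1: 255 and 13).
- Calcium: design effect 1 + 19 × 0.5 = 10.5. Unclustered n = 28.28 per arm; × 10.5 = 296.9; ÷ 20 = 14.85 clusters per arm (Table 1: 294 and 14.7).

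Both agree within rounding and confirm that the printed totals are per-arm figures.

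**Step 2. Double.** Activity: 2 × 12.8 = 25.6, so 26 workplaces, 13 per arm. Calcium: 2 × 14.85 = 29.7, so 30 workplaces at ICC 0.5. The article prints neither figure; both follow from the error that it discloses.

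**Step 3. Unadjusted power with 16 workplaces of 20 (160 per arm).** SE = SD × √(2 × design effect/160).

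- Activity at ICC 0.05: SE = 150 × √(2 × 1.95/160) = 23.4 minutes; 60/23.4 = 2.56. Power is 73% (normal) or 66% (noncentral t, 14 df, matching a cluster-level t-test on 16 means).
- Calcium at ICC 0.5: SE = 290 × √(2 × 10.5/160) = 105.1 mg; 250/105.1 = 2.38. Power is 66% (normal) or 60% (t).

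**Step 4. How far below its assumed value must each ICC lie for 16 workplaces to give 90% power?**

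| Outcome | ICC assumed | Largest ICC giving 90% (normal) | Largest ICC giving 90% (t, 14 df) |
|---|---|---|---|
| Calcium, 250 mg | 0.5 | 0.245 | 0.204 |
| Activity, 60 min | 0.05 | 0.011 | 0.003 |

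For calcium, a value about half the assumed one or less suffices, and the assumed value is described as conservative. For activity, the ICC must be less than a quarter of a value taken from published studies.

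**Step 5. Sensitivity for activity.** Unadjusted power for 60 minutes (t to normal): 86–91% at ICC 0.01, 81–86% at 0.02, 66–73% at 0.05, 50–56% at 0.10.

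**Step 6. Compare with the article's own disclosure.** The printed 85 minutes is about 60 × √2 = 84.9. For 16 clusters of 20 at ICC 0.05, the difference detectable with 90% power is 75.9 minutes (normal) or 81.7 minutes (t). All three exceed 60 minutes, so the disclosure and the overpowered statement in the same paragraph do not agree for activity.

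**Step 7. How much could the calcium ICC have inflated the cluster count?** The larger requirement governs. With a smaller calcium ICC, activity's undoubled 13 would have set the number, giving 14 once the arms are evened. On the plan's own rule, at most two of the 16 clusters are attributable to calcium's large ICC.

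**The case against.** Several counter-arguments have force.

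- **The Limitations sentence is conditional.** It speaks of outcomes without published ICCs, and the sentence before it separates limited from absent values. On that reading it covers calcium only and agrees with Table 1. The inflation sentence is hedged and concerns the adopted number, which calcium did set. This stands: the Limitations wording is loose but not plainly wrong. The clause in the Sample size calculation section has no such condition, so the point rests there.
- **The shortfall is disclosed.** The article admits the missed doubling and gives 85 minutes, which is if anything pessimistic. The Limitations section also allows that the study may be underpowered to account for confounding, and commits to publishing observed ICCs, including for activity, with a retrospective power calculation. This rules out any reading that the shortfall was hidden. It does not repair the reason given for accepting it, and the underpowering caveat concerns confounding, not activity or the missed doubling.
- **Baseline adjustment may restore power.** The two-stage analysis adjusts for baseline and other covariates. Assume, purely for illustration, equal variance reduction at both levels and ICC 0.05. A baseline–outcome correlation of 0.5, 0.6 or 0.7 would then give 79–84%, 85–89% or 92–95% power. The article gives no correlation and does not rely on this gain, so adequate power is not shown. Absence of any reserve is not shown either.
- **The published value may itself be cautious.** A reader might infer that 0.05 is a central estimate with no margin. The footnote does not say where 0.05 lies among the published estimates, so that inference is not supported.

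**Conclusion.** The concern holds in limited form. The statement that the ICCs were very conservative and the study overpowered is supported by Table 1 for calcium intake and unsupported for physical activity. On the plan's own inputs, activity needs about 26 workplaces for 90% power at 60 minutes. The 16 randomised give about 66–73% unadjusted power, a 27–34% chance of missing the target effect if it is real. Without adjustment, 90% would need a true ICC of about 0.01 or less.

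These figures assume a two-sided test, equal clusters of 20 analysed, and Table 1's SD and ICC. They take no credit for baseline adjustment. They do not show that the design has no reserve for activity, or that the trial will in fact be underpowered for it. What they show is that the stated reassurance does not follow for this outcome, and that it conflicts with the 85-minute figure in the same paragraph.

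**What to change.** 1. In the paragraph after Table 1, limit the clause on conservative ICCs and overpowering to calcium intake.
2. In the Limitations section, limit the sentences on large ICCs and a possibly inflated cluster count to calcium intake.
3. For physical activity, state that the ICC of 0.05 was based on published studies and that, at this value, 16 workplaces of 20 give about 66–73% unadjusted power for 60 minutes. Any gain from baseline adjustment should be described as unquantified unless a correlation is supplied. Do not call 0.05 a central value or say that no reserve exists.
4. State that a non-significant activity result will be interpreted from its confidence interval against 60 minutes, not as absence of effect.

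The cost is rewording in two sections and a less favourable stated position on activity. No participants are added, and neither the design nor the analysis method changes.

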## Abbreviations

ICC: Intraclass correlation coefficient; MET: Metabolic equivalent of task; MET-hour: Metabolic equivalent of task per hour; RDA: Recommended daily allowance
